## 9.3 STATISTICAL ANALYSIS

9.3.1 SUMMARY OF THE BACKGROUND INFORMATION

The categorical variables (gender, medical history, past medical history, and so forth) are summarized using the frequency and proportion. The continuous variables (age, height, weight, and so forth) are summarized using the average, standard deviation, median, quartile range, minimum, and maximum. All variables are shown in each group and stratification: the number of weeks after birth.

9.3.2 PRIMARY ENDPOINT ANALYSIS

Statistical analysis will be performed following the intention to treat (ITT) principle, where participants will be analyzed as they were randomized, not as they were treated. The primary analysis is performed using FAS, and secondarily using PPS. The participants who have missing data for the presence of IgE-mediated hen’s egg allergy are defined as having IgE-mediated hen’s egg allergy and included in the FAS analysis. The participants who have missing data for the presence of IgE-mediated hen’s egg allergy are excluded from the PPS analysis. To verify the study hypothesis, “the aggressive intervention group has lower prevalence of IgE-mediated hen’s egg allergy compared to the conventional treatment group”, the main comparison is the null hypothesis that the percentage of IgE-mediated hen’s egg allergy is higher in the aggressive treatment group than in the conventional group" and the alternative hypothesis is that the percentage of IgE-mediated hen’s egg allergy is lower in the aggressive treatment group than in the conventional group. The *p* value is calculated by the difference in percentage with a one-sided test. The significance level is 0.025. The difference and ratio of these proportions and their 95% confidence intervals for each intervention group will also be calculated.

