## 5.3 RANDOMIZATION AND STRATIFICATION

Stratified block assignment with the number of weeks after birth (7 to 10 weeks, 11 to 13 weeks) as the factor in the order of registration is performed and participants are randomly assigned to the “aggressive intervention group” or “conventional treatment group” in a ratio of 1:1.

Justification for stratification

At an early onset, atopic dermatitis tends to be severe, so the number of weeks after birth was assigned as an adjustment factor.

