5.9.2 STUDY DISCONTINUATION

Participants can discontinue the study if they meet any of the criteria described below:

Study physicians determine that the participants are unable to continue study treatment in PACI study due to exacerbation of AD

Participation in the study is discontinued because of adverse events

Proxies (parents or legal guardians) withdrawal from the study

Participants are unable to attend a study visit because of moving or hospital transfer

Death during study participation

PACI study is terminated

Study physicians determine that it is difficult to continue the study intervention for participants for reasons other than the above

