# 9 STATISTICS

## 9.1 SAMPLE SIZE

For sample size calculation, the proportion of egg allergy in early aggressive intervention and conventional treatment groups are estimated to be 20% and 30%, respectively. With a one-sided significance level of 0.025, 581 participants are needed to provide 80% statistical power. One interim analysis examining efficacy and safety is planned when almost half the participants are finished their trial assessment. Considering the interim analysis, 614 participants are needed. We expect a drop of about 5%, and set the target number of study participants to 650.

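### Stopping study treatment is not separated from leaving the study, and missing challenge results are scored as egg allergy, so unequal withdrawal can bias the primary comparison in either direction

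*Protocol*

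**What the plan says.** Section 9.3.2 makes the Full Analysis Set (FAS) primary and fixes the handling of a missing outcome in it: "The participants who have missing data for the presence of IgE-mediated hen’s egg allergy are defined as having IgE-mediated hen’s egg allergy". In the Per Protocol Set (PPS), infants with a missing outcome are dropped instead. Section 9.3.4 runs the interim analysis of the primary endpoint in the same way as 9.3.2, so the rule also feeds the efficacy and futility boundaries.

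Section 5.9.2, headed as study discontinuation, includes "Study physicians determine that the participants are unable to continue study treatment in PACI study due to exacerbation of AD" and "Participation in the study is discontinued because of adverse events", together with a physician's judgement that the intervention is hard to continue. Section 5.1.3 mentions criteria for discontinuing study treatment, but 5.9.2 is the only such list. Section 5.9.1 ties study completion to the 28-week OFC. No section schedules that OFC for an infant whose treatment has stopped.

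Under section 5.4, parents and treating investigators are not blinded; only the physicians who perform the OFC and examine the skin are.

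On design, section 9.1 says "the proportion of egg allergy in early aggressive intervention and conventional treatment groups are estimated to be 20% and 30%, respectively". It continues: "With a one-sided significance level of 0.025, 581 participants are needed to provide 80% statistical power"; "Considering the interim analysis, 614 participants are needed"; "We expect a drop of about 5%, and set the target number of study participants to 650". Allocation is "in a ratio of 1:1" (section 5.3).

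**The concern.** Taken together, 5.9.2 and 9.3.2 allow an open-label decision about treatment to become a primary event without a challenge being done. The arms differ in steroid exposure (sections 5.6.3 and 5.6.4), so flares and adverse reactions need not lead to withdrawal equally often. Scoring missing as allergic leaves the null comparison undisturbed only if missingness is equal by arm. If the conventional arm loses more infants, the rule adds apparent benefit. If the aggressive arm loses more, it hides real benefit. This affects the single confirmatory test, and an OFC result that was not collected cannot be recovered later.

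**Working it through.** **The plan's own figures.** With two proportions, unpooled variance, one-sided 0.025 and 80% power: 2 × (1.960 + 0.842)² × (0.20×0.80 + 0.30×0.70) / 0.10² = 580.8, matching 581. One look at half information, with O'Brien–Fleming-type alpha and beta spending and non-binding futility, inflates this by 1.056 to 613.5, matching 614. Then 614/0.95 = 646.3, consistent with a target of 650 (325 per arm). These figures are not in dispute.

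**Inputs.** From the protocol: 325 per arm, one-sided 0.025, 20% v 30%, about 5% drop-out overall. Assumed: the split of missing outcomes between arms, missingness unrelated to allergy within an arm, all 325 per arm in the FAS, and for the null case 25% true allergy in both arms (midway between 20% and 30%).

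**Formulas.** The scored rate in an arm with true rate p and missing fraction m is q = m + (1-m)p. With equal p, the expected difference (conventional minus aggressive) is (1-p)(m_C - m_A). That is 0.8 point per point of gap at p = 20% and 0.7 at p = 30%. SE = √{[q_A(1-q_A) + q_C(1-q_C)]/325}. The fixed-sample rejection probability is Φ(difference/SE - 1.96).

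**No true effect (25% in both arms)**

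| Missing, aggressive/conventional | q_A | q_C | Difference | SE | One-sided type I error |
|---|---|---|---|---|---|
| 5%/5% | 0.2875 | 0.2875 | 0 | 0.0355 | 0.025 |
| 4%/6% | 0.2800 | 0.2950 | 0.015 | 0.0355 | 0.06 |
| 3%/7% | 0.2725 | 0.3025 | 0.030 | 0.0355 | 0.13 |
| 7%/3% | 0.3025 | 0.2725 | -0.030 | 0.0355 | 0.003 |

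With the two-look boundaries applied, 3%/7% gives 0.12. At 3%/7% the fixed-sample result is 0.16 if the true rate is 20% and 0.11 if it is 30%.

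**True effect, 20% v 30%**

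| Missing, aggressive/conventional | q_A | q_C | Difference | SE | Power |
|---|---|---|---|---|---|
| none | 0.200 | 0.300 | 0.100 | 0.0337 | 0.84 |
| 5%/5% | 0.240 | 0.335 | 0.095 | 0.0353 | 0.77 |
| 4%/6% | 0.232 | 0.342 | 0.110 | 0.0352 | 0.88 |
| 6%/4% | 0.248 | 0.328 | 0.080 | 0.0354 | 0.62 |
| 7%/3% | 0.256 | 0.321 | 0.065 | 0.0354 | 0.45 |

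**Missing results excluded instead.** At 5%/5%, n = 325 × 0.95 = 308.75 per arm, SE = √(0.37/308.75) = 0.0346 and power is 0.82. At 7%/3% it is also 0.82, and under the null at 3%/7% the type I error is 0.025. The inflation from 614 to 650 treats drop-outs as lost, while 9.3.2 counts them as allergic. Even with no imbalance, the rule therefore costs about 5 points of power (0.77 against 0.82).

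**The case against.** The strongest reply has four parts.

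- **The text does not say these infants miss the OFC.** A reader might infer that everyone who stops treatment leaves before the challenge. The documents do not support that as a fact: 5.9.2 says participants can discontinue, 5.1.3 runs study duration to the primary assessment, and 9.3.2 analyses infants as randomised. What stands is that the two kinds of stopping are not separated and nothing requires the OFC. Section 11.5, which has physicians stop the study when related adverse events occur, points towards loss of follow-up.
- **Imbalance may be limited.** Conventional-arm infants without remission may switch regimen from week 8, recorded as a deviation. Both arms may use the stronger rescue steroid. The FAS omits infants with no data after treatment starts. These features can narrow the gap, but the switch is discretionary and does not cover earlier flares or adverse events.
- **The sizes rest on assumed splits.** This is correct. At 5%/5% there is no inflation of type I error. Infants who leave may also be allergic more often than the rest; the bias per missing infant would then be smaller.
- **The PPS excludes missing outcomes.** It does, but it also drops significant deviators, so it is not a clean check of this rule.

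A reader might also infer that filling in a fixed value makes the confidence interval too narrow. It does not here: scoring missing as allergic moves the rates towards 50% and keeps n at 325. At 25% in both arms and 3%/7% missing, the SE is 0.0355, against 0.0349 from observed results only. The problem is bias.

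**Conclusion.** The point holds. The protocol fixes a primary-analysis rule that is not reliably conservative, and its discontinuation section leaves open a route by which treatment decisions feed that rule. A missingness gap converts at (1-p), about 0.7 to 0.8 point per point, not one for one. Its direction depends on which arm loses more infants, so the documents do not support reading the rule as favouring the aggressive arm in particular.

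Within the stated 5% overall, a 4%/6% split takes one-sided type I error to about 0.06 and a 3%/7% split to 0.12 to 0.13. A 7%/3% split cuts power to 0.45. These sizes rest on assumed splits, on missingness unrelated to allergy, and on a 25% true rate for the null case. The fall in power to 0.77 needs no imbalance, only the planned 5% in each arm and the protocol's own rates. Most outcomes would still be observed challenges, so the primary result is not simply a comparison of withdrawal rates.

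**What to change.** 1. In section 5.9.2, separate stopping study treatment from leaving the study. Invite every randomised infant to the already planned 28-week OFC and blood test unless consent is withdrawn or the OFC is judged unsafe.
2. Report missing primary outcomes by arm and reason.
3. In section 9.3.2, do not let scoring missing as allergic stand alone as the primary result. Pair it with an analysis that does not score missing as allergic: observed OFC results, or multiple imputation by arm from age stratum, EASI and baseline egg-white IgE. Add a tipping-point table by arm. The choice of imputation model is open to debate, since it assumes that the recorded data explain the missingness and specific IgE is measured only at entry and at 28 weeks. Step 1 does not depend on it.

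The cost is a change of protocol wording, one already planned visit for a few families who stopped treatment, and some analysis work. No additional participants are needed.

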## 4.1 INCLUSION CRITERIA

Infants (7–13 weeks old) who develop an itchy rash within the previous 28 days and receive a diagnosis of AD based on the U.K. Working Party’s diagnostic criteria

Justification for inclusion criteria

All infants with AD, including those with a family history of AD, will be included. The reason is that we would like to apply the study results for all infants with AD, not only for infants with a specific family background. As the U.K. Working Party’s diagnostic criteria is validated and has been widely used in various intervention studies internationally (66), we will apply the criteria in our study as well. Martin *et al.* reported that 20% of infants at 1 year of age who had a history of eczema received a diagnosis of FA (38). There were 50.8% of infants (95%CI: 42.8, 58.9) with early eczema onset (<3 months) who required doctor-prescribed topical corticosteroid treatment who developed challenge-proven FA. Shoda *et al.* demonstrated that in each age stratum (by month), infants with onset of eczema within the first 1–2 months after birth had the highest risk of FA at 3 years of age (aOR 6.61; 95%CI: 3.27, 13.34; *p*<0.001) (14). Infants who develop AD in early infancy are considered to have a higher risk for later FA and the defined target population in the PACI study is infants at the age of 7–13 weeks. We will exclude infants less than 6 weeks of age because differential diagnosis is difficult between AD and other skin diseases such as seborrheic dermatitis. Infants with AD at the age of 7 weeks and over are target populations because AD diagnosis is available.

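### Randomisation is stratified by age, but the primary test in 9.3.2 is written as a simple difference in percentages that does not use the strata

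*Protocol*

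**What the plan says.** Protocol 5.3 describes the allocation as "Stratified block assignment with the number of weeks after birth (7 to 10 weeks, 11 to 13 weeks) as the factor", "in a ratio of 1:1". The reason given is that early-onset disease "atopic dermatitis tends to be severe, so the number of weeks after birth was assigned as an adjustment factor". Protocol 4.1 connects early onset to the outcome: "Infants who develop AD in early infancy are considered to have a higher risk for later FA".

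Protocol 9.3.2 gives the primary method. The p "value is calculated by the difference in percentage with a one-sided test", at a significance level of 0.025. On estimation it adds: "The difference and ratio of these proportions and their 95% confidence intervals for each intervention group will also be calculated". It mentions no stratum, stratified weighting or covariate. Section 9.3.4 carries the 9.3.2 analysis over to the interim.

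Within section 9 the age groups appear only in the baseline tables of 9.3.1: "All variables are shown in each group and stratification: the number of weeks after birth". The sentence that leaves method details to the statistical analysis plan is in 9.3.3, which covers secondary endpoints.

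**The concern.** The Protocol treats age as important enough to balance at randomisation, and argues elsewhere that early onset raises food-allergy risk. Stratified blocks remove the chance imbalance in age between arms. A test that ignores the strata still charges for that imbalance in its standard error. If age predicts egg allergy, the standard error is too large, the test rejects less often than its nominal level under the null, and some power is lost. The same statistic feeds the interim efficacy and futility comparisons.

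What is at stake is precision and agreement between design and analysis. The false-positive rate is not at risk.

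**Working it through.** **1. Is the plan built on an unstratified test?** Inputs from Protocol 9.1: 20% v 30%, one-sided 0.025, power 80%, stated N = 581. The unstratified two-proportion formula with unpooled variance gives

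n per arm = (1.960 + 0.842)² × (0.30×0.70 + 0.20×0.80) / 0.10² = 7.849 × 0.37 / 0.01 = 290.4,

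so N = 580.8, which rounds up to 581. The stated figure reproduces exactly without strata, which supports reading 9.3.2 as unstratified.

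**2. Size of the unstratified test, by formula.** Assume two equal strata, both arms at 30% overall (the null), and stratum rates of 0.30 ± d/2. The unstratified test uses a per-infant variance of 0.30 × 0.70 = 0.21. With allocation balanced within strata, the variance that actually applies is 0.21 − d²/4. The effective critical value is therefore 1.960 / √[(0.21 − d²/4)/0.21].

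| Gap d | 0.21 − d²/4 | Effective critical value | One-sided size |
|---|---|---|---|
| 0 | 0.2100 | 1.960 | 0.0250 |
| 10 points | 0.2075 | 1.972 | 0.0243 |
| 20 points | 0.2000 | 2.008 | 0.0223 |
| 30 points | 0.1875 | 2.074 | 0.0190 |

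**3. Size and power by simulation.** N = 614 (Protocol 9.1), fixed design without the interim look, equal strata, 30% v 20% overall with a common odds ratio, 400,000 trials per scenario. The pooled z-test is compared with Cochran-Mantel-Haenszel (CMH) without continuity correction. The gap is in conventional-arm rates and is an assumption throughout.

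| Gap | Size, unstratified | Size, CMH | Power, unstratified | Power, CMH | Gain (points) |
|---|---|---|---|---|---|
| 0 | 0.0251 | 0.0249 | 81.97% | 81.98% | 0.0 |
| 5 | 0.0247 | 0.0247 | 82.10% | 82.17% | 0.1 |
| 10 | 0.0240 | 0.0245 | 82.15% | 82.43% | 0.3 |
| 20 | 0.0222 | 0.0248 | 82.56% | 83.66% | 1.1 |
| 30 | 0.0191 | 0.0251 | 83.21% | 85.55% | 2.3 |

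The simulated sizes agree with step 2. A 30/70 split between the strata gives nearly the same results. CMH keeps its nominal size throughout and loses nothing when the strata do not differ.

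**4. Which gap is plausible?** No egg-allergy rate by age stratum is given. The nearest figures, in Protocol 1.2.4, are adjusted odds ratios for food allergy at 3 years of 6.61 (eczema onset at 1–2 months) and 4.69 (onset at 3–4 months). Their ratio is 6.61/4.69 = 1.41. Around 30% overall with equal strata, this corresponds to roughly 34% v 26%, a gap of about 7 points. The guide is indirect: it concerns any food allergy, at a later age, by age at onset. It points to the low end of the table, so the 30-point row is an extreme case.

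**The case against.** The strongest objection is that 9.3.2 names no test and never says unadjusted. A Mantel-Haenszel risk difference is also a difference in percentages, and the unseen statistical analysis plan could specify one. This stands as a limit: the unstratified reading is an inference. It is still the natural one. Section 9.3.2 sets out the primary method itself, the deferral to the analysis plan is in the secondary-endpoint section, and the sample size is unstratified.

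A reader might infer that 5.3 promises an adjusted analysis which 9.3.2 then breaks. The text does not go that far. The phrase "so the number of weeks after birth was assigned as an adjustment factor" justifies the allocation, and the reason given is severity of dermatitis. The link to food allergy comes from 4.1 and concerns age at onset. Section 4.1 requires the rash to have appeared within the previous 28 days, so entry age follows onset age to within four weeks. With strata only 28 and 21 days wide (section 3), however, the two groups overlap in age at onset. That weakens any gap between them.

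The benefit is also small at gaps near those the Protocol's own figures suggest. That stands too, and it limits how much weight the point can bear.

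**Conclusion.** The point holds as a modest, free improvement. The trial randomises by age group, and the primary test as written does not use the groups. Over assumed gaps of 0 to 30 points, the unstratified test's one-sided size falls from 0.025 to about 0.019, and stratification adds about 0 to 2.3 points of power (0.1 to 0.3 at gaps of 5 to 10). These figures rest on the assumed gap, a common odds ratio, complete data and no interim look.

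Three stronger readings are not supported:

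- **The primary test is invalid.** It is not. Its error is on the conservative side.
- **Ignoring the strata leaves the trial short of its 80% power.** It does not. In the scenarios above the unstratified test has about 82% to 83% power at N = 614.
- **Omitting baseline EASI and egg-white-specific IgE is an error.** Both are collected at Day 0, but no section commits to adjusting for them. Adjustment might improve precision, by an amount the Protocol gives no basis for stating.

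**What to change.** In Protocol 9.3.2, state that:

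- the primary one-sided test is Cochran-Mantel-Haenszel, stratified by age at entry as randomised (7–10, 11–13 weeks), and whether a continuity correction is used;
- the treatment effect is the Mantel-Haenszel risk difference and risk ratio, each with a 95% confidence interval;
- the unstratified difference is reported as supportive.

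In 9.3.4, state that the interim comparison uses the same stratified test. If the analysis plan already specifies this, align the Protocol wording with it. Adjustment for baseline EASI and egg-white-specific IgE can be added as an optional secondary analysis.

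The cost is a few sentences. No new data or larger sample is needed, since CMH matches the unstratified test when the strata do not differ. The choice should be fixed before anyone sees unblinded results.

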9.3.3 SECONDARY ENDPOINTS ANALYSIS

All secondary endpoints will be analyzed using FAS and secondarily using PPS. The details of statistical methods are described in the statistical analysis plan.

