Additional skin rash treatment

Participants are to apply TCSs as additional treatment as described below:

| Area | Face | | Body except scalp and face | | | Scalp |
| --- | --- | --- | --- | --- | --- | --- |
| Severity of skin rash | Less mild | Mild, moderate, and severe | Less mild | Mild and moderate | Severe | Any severity |
| Registration day (Day 0) of the study  to 28 weeks of age | Without additional treatment | Almeta^®^ ointment  every day until rash remission  once a day | Without additional treatment | Almeta^®^ ointment every day until rash remission  once a day | Rinderon^®^-V  ointment  every day until rash remission  once a day | Rinderon^®^-V valerate lotion until rash remission  once a day |

Note:

When skin rash recurs, participants should re-apply TCSs on their body daily until they obtain remission of the skin rash.

If participants do not have remission from the skin rash by applying Rinderon^®^-V for 7 days, they are permitted to use mometasone (Fulumeta^®^).

When ointment is removed by washing or wiping, it can be re-applied.

If study physicians judge participants do not obtain remission to AD 8 weeks after the entry, they can change the treatment to aggressive intervention treatment, which is treated as a deviation.

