## 8.2 SECONDARY ENDPOINTS

EFFICACY ENDPOINTS

1. Food challenge test scores at the age of 28 weeks
2. Total IgE antibody titer in serum at the age of 28 weeks
3. Egg white, ovomucoid, milk, soy, wheat, and peanut-specific IgE antibody titers in serum at the age of 28 weeks
4. Egg white, ovomucoid, milk, soy, wheat, and peanut-specific IgG4 antibody titers in serum at the age of 28 weeks
5. Eczema Area and Severity Index (EASI) scores at 2, 4, and 8 weeks after study entry and at the age of 28 weeks
6. Patient Oriented Eczema Measure (POEM) scores weekly through the study
7. Percentage of disease-free days throughout the study
8. Dose of rescue medication used throughout the duration of the study
9. Infants’ Dermatitis Quality of Life Questionnaire (IDQoL) at 2, 4, and 8 weeks after study entry and at 28 weeks of age
10. Family Impact of Childhood Eczema Questionnaire (DFI) at 2, 4, and 8 weeks after study entry and at 28 weeks of age
11. Cumulative incidence of IgE-mediated FA assessed by a doctor’s interview during the study
12. Cumulative incidence of wheezing assessed by a doctor’s interview during the study

Justification for secondary endpoints (efficacy)

(1) Scoring of the food challenge test has already been recommended in the American Academy of Allergy, Asthma & Immunology – European Academy of Allergy and Clinical Immunology PRACTALL consensus report (65).

(2) (3) To evaluate allergy sensitization

(4) To evaluate immune tolerance against hen’s egg

(5) (6) To evaluate the activity and severity of AD

(7) (8) To evaluate the disease control

(9) (10) To evaluate the QoL

(11) To evaluate the prevalence of other IgE-mediated FA except hen’s egg

(12) To evaluate the prevalence of signs related to asthma

SECONDARY ENDPOINTS (SAFETY)

1. Serious adverse events
2. Adverse drug reactions
3. Salivary cortisol concentrations at 2, 4, and 8 weeks after study entry and at the age of 28 weeks
4. Body weight and body height at the age of 28 weeks

Justification for secondary endpoints (safety)

(1) (2) To evaluate safety of the study drugs

(3) To evaluate the effect on adrenal function by adverse drug reactions to TCSs

(4) To evaluate the effect of adverse drug reactions to TCSs on growth

ADHERENCE EVALUATION

(1) TCS adherence index in accordance with the protocol

(2) Dose of TCS used during the study

Justification for adherence evaluations

(1)(2) To evaluate adherence to the protocol

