## 9.2 ANALYSIS SET

The following data set is used for analysis. The target analysis of the primary endpoint of efficacy is defined as Full Analysis Set (FAS).

1. Full Analysis Set (FAS)

The group excluding the participants as follows from all the participants who are randomized

- - Participants who have never received intervention
  - Participants who have not yielded data after the start of the study treatment
  - Participants who are found to have violated eligibility criteria after received intervention t

1. Per Protocol Set (PPS)

Of the FAS, the group consisting of participants without significant deviation from the implementation plan

1. Target group for safety analysis

The group consisting of all participants who have undergone the study treatment at least once

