## 12.2 DEVIATIONS

12.2.1 UNEXPECTED DEVIATION

Unexpected deviations are not protocol violations (12.1) nor acceptable deviations (12.2.2). If the study physician judges that it is not possible to maintain remission of atopic dermatitis in the standard treatment group, it will be possible to start the same protocol as the early aggressive treatment group later than 8 weeks after enrollment, and such a case is defined as a deviation.

Deviations are described in central monitoring reports. If there are many specific deviations, the results of the deviations will be mentioned in the final report.

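### Section 9.3.3 sends the safety endpoints to FAS and PPS, bypassing the safety group of 9.2; if arms are kept as randomised, late effects in switched infants dilute any harm difference

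*Protocol*

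**What the plan says.** Three parts of the protocol bear on who enters the safety analysis and in which arm.

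- **Analysis set.** Section 8.2 lists serious adverse events, adverse drug reactions, salivary cortisol (weeks 2, 4 and 8 and age 28 weeks) and weight and height at 28 weeks as safety endpoints within the secondary endpoints. Section 9.3.3 then says: "All secondary endpoints will be analyzed using FAS and secondarily using PPS". Section 9.2 also defines a target group for safety analysis: "The group consisting of all participants who have undergone the study treatment at least once". No part of 9.3 assigns an endpoint to that group.
- **Grouping.** The one rule is in 9.3.2, under the primary endpoint: "participants will be analyzed as they were randomized, not as they were treated".
- **Switching.** The notes to the conventional regimen in 5.6.4 say of infants without remission 8 weeks after entry that study physicians may act as follows: "they can change the treatment to aggressive intervention treatment, which is treated as a deviation". Section 12.2.1 says of the conventional arm: "it will be possible to start the same protocol as the early aggressive treatment group later than 8 weeks after enrollment". It also calls this a deviation.

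The stated purpose of the cortisol endpoint in 8.2 is: "To evaluate the effect on adrenal function by adverse drug reactions to TCSs".

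**The concern.** There are two linked problems.

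First, 9.2 and 9.3.3 do not fit together. A safety group is defined and left unused, while every secondary endpoint, safety included, goes to sets built for efficacy. The FAS excludes infants found after treatment began to have violated eligibility. Their events belong in a safety analysis and would be lost from it.

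Second, the protocol does not say in which arm a switched infant's later safety results are counted. If the as-randomised rule of 9.3.2 is carried over, effects that arise under the aggressive regimen are recorded as conventional-arm results. Should that regimen cause more harm, the two arms would look more alike than the two regimens are. Detecting steroid effects on the adrenal axis and on growth is why these endpoints exist, so a shift towards no difference is the unfavourable direction. Section 9.3.4 includes safety endpoints in the interim analysis, so the monitoring committee could be shown the same comparison.

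**Working it through.** The protocol gives no switch rate, no safety event rate and no safety power, so it has no figure of its own to reproduce. The check sets the texts side by side and then scales the dilution under stated assumptions.

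**1. FAS against the safety group (9.2).** The safety group takes everyone treated at least once. The FAS starts from all randomised infants and removes those never treated, those with no data after treatment start, and those found ineligible after treatment. The third exclusion takes out treated infants who may have reportable events. The PPS lies inside the FAS, so it cannot bring them back.

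**2. Which safety results a switch can reach.**

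| Safety result (8.2) | Can it fall after a switch? |
| --- | --- |
| Cortisol, weeks 2 and 4 | No |
| Cortisol, week 8 | Normally no, if sampled before the switch |
| Cortisol, 28 weeks of age | Yes |
| Weight and height, 28 weeks of age | Yes |
| Serious adverse events, drug reactions | Only those with onset after the switch |

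**3. Time left after a switch.** Inputs: entry at age 42 to 90 days (weeks 7 to 13 in the section 3 age table), 28 weeks = age 189 to 195 days (same table), earliest switch about Day 56, visit window ±14 days (6.1).

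- Without the window: shortest 189 − (90 + 56) = 43 days; longest 195 − (42 + 56) = 97 days.
- With the window: shortest 43 − 14 = 29 days; longest 97 + 14 = 111 days.
- Total follow-up with the window: 189 − 14 − 90 = 85 days to 195 + 14 − 42 = 167 days. The post-switch share is 29/85 = 34% to 111/167 = 66%. These are extremes of entry age and window, with the earliest possible switch.

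**4. Dilution under as-randomised grouping.** Let D be the difference between arms if nobody switched, x the share of the conventional arm that switches, and f the share of D that a switcher has taken on by the time of assessment. The conventional-arm mean or risk moves by x·f·D towards the aggressive arm, so

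observed difference = D·(1 − x·f).

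| x (assumed) | f = 1 | f = 0.5 |
| --- | --- | --- |
| 5% | 0.95 D | 0.975 D |
| 10% | 0.90 D | 0.95 D |
| 20% | 0.80 D | 0.90 D |

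With the full excess effect (f = 1), the affected differences shrink by 5% to 20%; with half of it, by 2.5% to 10%.

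**5. A sense of scale.** Assume a drug-reaction risk of 10% against 5% and 307 infants per arm (614/2), tested one-sided at 0.025. Power is 65% without switching and, at f = 1, 60%, 55% and 45% with 5%, 10% and 20% switching. The risks are assumed and the protocol specifies no such test; this is illustration only.

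**The case against.** The case on the other side has five parts.

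- **The grouping rule is not stated for safety.** The as-randomised sentence stands under the primary endpoint, and naming the FAS fixes who is included, not how they are grouped. This stands. A reader might infer that the protocol plans to compare safety by randomised arm; that is a plausible reading, since no other rule exists, but it is not what the text says.
- **The SAP may settle it.** Section 9.3.3 leaves the detail of methods to the SAP, which was not available for this point, and safety grouping and table layouts are ordinary SAP content. This stands for the grouping rule. It does not remove the mismatch between 9.2 and 9.3.3, because the protocol itself fixes the analysis set.
- **As-randomised comparison of safety is legitimate.** It contrasts two strategies, one of which allows escalation, and it keeps randomisation. This stands. A reader might infer that as-randomised safety tables are wrong and should be replaced by grouping on treatment received. The documents do not support that: regrouping would move infants selected for uncontrolled dermatitis into the aggressive group.
- **The PPS may exclude switchers.** It might, but 9.2 removes only significant deviations and the protocol does not say whether a switch is one. If switchers are removed, their later events leave the comparison altogether.
- **The size is conjecture.** No switch rate is given, and f is uncertain in both directions. Infants whose rash persists would in any case continue daily topical steroids under 5.6.4, which lowers f. Switchers would start the intensive daily phase later, nearer the 28-week sample, which could raise it for cortisol. A reader might go on to assume a doubled effect and a shrinkage of up to 40%; nothing in the protocol supports that factor.

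**Conclusion.** The point holds in a limited form. The firm part is documentary: 9.3.3 sends the safety endpoints to FAS and PPS, 9.2 defines a safety group that is never used, and the FAS drops treated infants with eligibility violations.

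The second part is conditional. If as-randomised grouping carries over to safety, post-switch drug reactions and serious adverse events, and 28-week cortisol and growth in switchers, count as conventional-arm results and pull any harm difference towards zero. It would be wrong to extend this to the safety endpoints as a whole, since everything observed before the switch is unaffected.

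The size is unknown. A reduction of 5% to 20% in the affected differences rests on two assumptions: that 5% to 20% of the conventional arm switch, and that they take on the full excess effect. The primary and other efficacy analyses are not in question. This is an inexpensive improvement that should be made.

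**What to change.** Amend 9.3.3 as follows.

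1. Assign the safety endpoints of 8.2 to the safety analysis group of 9.2, and confine the FAS and PPS rule to the efficacy endpoints.
2. State that the safety comparison by randomised arm is kept.
3. Add beside it, as descriptive tables:
   - serious adverse events and adverse drug reactions by regimen in use at onset, with conventional-arm time ending at the switch, post-switch events in their own column, and infant-weeks as the denominator;
   - 28-week salivary cortisol, weight and height for switchers, shown separately.
4. Leave the efficacy endpoints as randomised.

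The cost is a few sentences and some extra tables. The data are already collected: 7.2 records the day an event occurs, 6.1 records days of steroid application daily, and a switch is documented as a deviation. The downside is that the by-regimen columns are not randomised comparisons, since switchers are selected for poor control of their dermatitis. The tables should say so and carry no test between columns.
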